### Intervention

#### Control Group

The subjects in the control group will be given health education and maintain their original lifestyle. Control subjects will be given a monthly uric acid popular science lecture, such as the relationship between hyperuricemia and gout, diet control of hyperuricemia patients, and correction of poor lifestyles. During the study period, high-purine diets will be banned.

#### Low-Intensity Exercise Group

Participants in the low-intensity exercise group will be intervened at Shanghai University of Sport at 57-63% of the maximum heart rate (220-age) (17). The exercise frequency will be 30 minutes a day, 5 days a week, for a period of 12 months. The subject will wear a heart rate monitor during exercise to monitor exercise intensity. In the first 2-4 weeks, subjects will exercise for 15-30 minutes at a maximum heart rate of <57%. Then, the subject’s exercise intensity will gradually increase to 57-63% of the maximum heart rate, and the time will be increased to 30 minutes. In addition, the low-intensity exercise group will maintain the same health education and prohibition of high-purine diet as the control group.

#### Moderate-Intensity Exercise Group

Participants in moderate-intensity exercise group will be intervened at Shanghai University of Sport at 64-76% of maximum heart rate (220 - age) (17). The exercise frequency will be 30 minutes a day, 5 days a week, for a period of 12 months. The subject will wear a heart rate monitor during exercise to monitor exercise intensity. In the first 2-4 weeks, subjects will exercise for 15-30 minutes at 57-63% of their maximum heart rate. Then, the exercise intensity of the subjects will gradually increase to 64-76% of the maximum heart rate, and the time will be increased to 30 minutes. In addition, the moderate -intensity exercise group will maintain the same health education and prohibition of high-purine diet as the control group.

In the low-intensity exercise group and the moderate-intensity exercise group, all exercise sessions will be supervised by research staff. The exercise intensity, duration, heart rate and blood pressure before and after exercise, and adverse events during exercise will be recorded by study staff. The study participant retention is critically important and every effort will be made to increase participants’ adherence to their intervention and follow-up visit schedule. If the subject fails to participate in the study more than 3 times in a row, the researcher will call the subject to ask the reason and encourage the subject to continue participating in the study. During the research process, the researchers will also send personalized gifts to the participants to strengthen their enthusiasm.

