#### Adverse Events

All adverse events reported during the study will be recorded on the case report form (CRF). In this trial, adverse events will be defined as any unfavorable and unexpected signs, symptoms, or diseases related to the intervention, such as falls, fractures, dizziness, high blood pressure, palpitations, chest pain, and low blood sugar. Researchers will ask the subjects about the adverse events they have experienced before the start of the training and record all the adverse events of the intervention. Participants will receive calls every week and ask about any adverse events experienced. Subjects will also be required to self-report any adverse events throughout the study protocol. A serious adverse event (SAE) will be notified to the lead investigator within 24 hours. The chief researcher is responsible for managing the safety report. Any adverse events related to the intervention will be reported to the ethics review committee of the Shanghai Institute of Physical Education. Although the committee and the author are from the same institution, the members of the ethics committee are independent of the investigators. None of these investigators are members of the ethics committee.

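### Adverse events and blood pressure are ascertained more intensively in the two exercise arms than in control, so exercise-versus-control counts of mild or measured events would tend to be inflated for exercise

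*Protocol article*

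**What the plan says.** All references are to the Protocol article.

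- **Exercise arms.** The sections on the low- and moderate-intensity groups set the same frequency: "The exercise frequency will be 30 minutes a day, 5 days a week, for a period of 12 months". For both arms, "all exercise sessions will be supervised by research staff", and at those sessions "heart rate and blood pressure before and after exercise, and adverse events during exercise will be recorded by study staff".
- **Control arm.** Under Control Group, the scheduled contact is educational: "Control subjects will be given a monthly uric acid popular science lecture". No adverse event enquiry or blood pressure measurement is stated for the lectures.
- **All arms.** Under Adverse Events, with no restriction by arm: "Participants will receive calls every week and ask about any adverse events experienced", and "Subjects will also be required to self-report any adverse events throughout the study protocol". Table 1 schedules adverse events and blood pressure at baseline and months 3, 6 and 12.
- **Tied to training.** The same section adds: "Researchers will ask the subjects about the adverse events they have experienced before the start of the training".
- **Definition and record.** Adverse events are "any unfavorable and unexpected signs, symptoms, or diseases related to the intervention, such as falls, fractures, dizziness, high blood pressure", with further examples that include palpitations. All reported events go onto the case report form, and no field for how an event came to light is mentioned.
- **Analysis.** Mathematical Statistics names no between-group comparison of adverse events.

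**The concern.** The issue is how events are found, not how they are defined. Two arms are watched and measured by staff up to five times a week. The third is asked once a week by telephone and measured at three follow-up visits. An event that shows itself through observation or measurement has more chances of being recorded in the exercise arms, even if it occurs equally often in all three.

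Blood pressure is the clearest case. A raised reading without symptoms will usually not surface in a telephone call or in self-report, so the common sources cannot close the gap for an event that the protocol itself lists.

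The trial is meant to inform physical activity guidance for people with hyperuricemia. If events from every source are tabulated together by arm, an excess under exercise could reflect exercise or more frequent looking, and the data could not separate the two unless the source had been recorded.

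**Working it through.** **Inputs from the document.** Five sessions a week of 30 minutes for 12 months in each exercise arm; blood pressure before and after each session; one call a week in all arms; post-baseline visits at months 3, 6 and 12 in all arms. Baseline is not counted, because randomization follows the baseline assessment.

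**Reproducing the plan's figure.** 5 × 30 = 150 minutes a week, as the Abstract states.

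**Scheduled adverse event contacts per person-year, excluding self-report**

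- Sessions: 5 × 52 = 260 at full attendance.
- Control: 52 calls + 3 visits = 55.
- Exercise: 260 + 55 = 315, and 315 / 55 = 5.7 times control.
- Exercise at an assumed 50% attendance: 130 + 55 = 185, and 185 / 55 = 3.4 times control.

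**Post-baseline blood pressure readings**

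- Control: 3.
- Exercise: 2 × 260 + 3 = 523 at full attendance.

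**Illustration for high blood pressure.** Assume that each reading has the same chance *p* of being flagged in every arm, that readings are independent, and that a flag counts as an event. The chance of at least one flag in *k* readings is 1 − (1 − *p*)^*k*. To leave out any effect of exertion, only pre-exercise session readings are counted: *k* = 260 + 3 = 263 for exercise at full attendance, 130 + 3 = 133 at 50% attendance, and 3 for control.

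| *p* (assumed) | Control | Exercise, 50% attendance | Exercise, full attendance |
|---|---|---|---|
| 0.1% | 0.3% | 12.5% | 23.1% |
| 0.5% | 1.5% | 48.7% | 73.2% |
| 1% | 3.0% | 73.7% | 92.9% |

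**Illustration for events that a call can pick up.** Let true risk be equal in all arms. Let *d* be the share of events found by calls, visits and self-report, and *g* the share of the missed events that sessions recover. The apparent risk ratio, exercise to control, is (*d* + (1 − *d*)*g*) / *d*. With *g* from 0.25 to 1:

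- *d* = 0.5: 1.25 to 2.0
- *d* = 0.7: 1.11 to 1.43
- *d* = 0.9: 1.03 to 1.11
- *d* = 1: 1.0, no bias

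**The case against.** - **Control is covered.** A reader might infer from the session recording that adverse events are not captured in control. The document does not support that: calls, required self-report and three follow-up visits apply to everyone. This stands, and it means the imbalance is one of intensity.
- **No harms comparison is planned.** Adverse events are neither a primary nor a secondary outcome, the hypotheses concern efficacy, and tabulation may be left to an analysis plan. This stands in part: the bias is conditional on someone comparing arms. But events are collected in every arm and will naturally be reported by arm, and side-by-side counts mislead without any test. An analysis plan can separate sources only if the case report form has captured them.
- **The percentages are not anchored.** This stands. The document gives no threshold for high blood pressure, does not say that a session reading becomes an adverse event, and requires events to be unexpected and related to the intervention. Readings within one person are correlated, which would shrink the gap.
- **The question about events before training is ambiguous.** It could be a single enquiry before the programme starts, matching the baseline entry in Table 1. This stands, and the counts above do not use it.
- **Restricting the comparison to common sources could hide harm.** A fall during a session is a genuine exercise harm and may not be repeated on a call. This stands, and is why all-source counts must stay visible.
- **Recording events at supervised exercise is ordinary safety monitoring.** Agreed. The point is how its yield is compared with control, not that it is done.

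**Conclusion.** The protocol fixes unequal ascertainment between exercise and control: up to 315 against 55 scheduled adverse event contacts a year, and up to 523 against 3 post-baseline blood pressure readings. Both maxima assume full attendance. At equal true rates, an exercise-versus-control tabulation pooling all sources would tend to be inflated for exercise. The problem is greatest for high blood pressure and other mild or measured events, and may be small or nil for symptomatic or serious ones.

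Two stronger readings are not supported. The first is that every harms comparison in the trial is biased: the low- and moderate-intensity arms share the same frequency, supervision and recording, so their comparison is not affected. The second is that the size of the bias is known: the percentages and risk ratios rest on assumed probabilities, independent readings and each flag counting as an event. The direction does not depend on the particular values chosen, although the bias vanishes if the common sources already find every event.

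The protocol's definition of adverse events by their relation to the intervention is a separate matter. Changing it would leave the unequal sources in place.

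**What to change.** In the Adverse Events section:

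1. Record on the case report form the source of each adverse event: session, weekly call, self-report or scheduled visit.
2. Use one identical script for the weekly call in all three arms.
3. Base the exercise-versus-control comparison on the common sources: calls, self-report and scheduled visits.
4. Report session-detected events and session blood pressure separately for the two exercise arms, as rates per session.
5. Show all-source counts by arm next to the common-source comparison, so that genuine exercise harms are not hidden.

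Session monitoring itself does not change. The cost is one field and one extra table. The downside is that events seen only at sessions do not enter the common-source comparison, although they remain in the session rates and the all-source counts. Trial Status places the trial before recruitment, so the field can be in place from the first participant; source could not be reliably reconstructed afterwards.

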### Outcome Assessment

Assessors will assess all primary and secondary outcomes at baseline, the 3rd, 6th, and 12th months. The evaluation process is shown in **Table 1**.

**Table 1 T1:** Schedule for data collection, the process of the assessments per visits.

Measures	Baseline	Intervention phase		
Time (months)	-12-0	3	6	12
Informed consent	✓			
Random grouping	✓			
Demographics and Past medical history	✓			
Anthropometric parameters (body weight, waist circumference, hip circumference, BMI)	✓	✓	✓	✓
Physiological indicators (blood pressure, grip, vital capacity, maximum oxygen)	✓	✓	✓	✓
Biochemical indicators (blood lipid, blood sugar, liver enzyme, creatinine, and blood urea nitrogen)	✓	✓	✓	✓
Serum uric acid	✓	✓	✓	✓
Adverse events	✓	✓	✓	✓
Completion of the test form				✓

#### Primary Outcomes

The concentration of SUA, the amount of concentration change (mg/dL), the rate of change (%), and the proportion of patients with SUA concentration ≤7.0 mg/dL (male) or ≤6.0 mg/dL (female) from baseline to the 3rd, 6th, and 12th months will be observed. Detection method: The blood samples will be collected between 8:00 am and 10:00 am. Subjects should keep fasting for 12 hours, that is, eating and drinking after 8 o’clock the day before blood collection is prohibited. Each subject will collect 5 mL of blood. The blood sample will be centrifuged at 3500r/min for 15min. The obtained serum samples will be stored in a refrigerator at -80°C and tested by Zhongshan Hospital with Fudan University.

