**Discussion:**

This study will evaluate the effect of 12-month low-intensity exercise and moderate-intensity exercise on HUA patients. We hypothesize that both low-intensity and moderate-intensity exercise would improve HUA as compared with no-exercise control, and that moderate-intensity exercise would be more effective than low-intensity exercise in improving HUA. These results can provide a basis for the current physical activity guidelines for HUA’s healthy lifestyle management.

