The symptoms of HUA are not obvious, which cause delay in treatment. The current management of HUA mainly includes medication and lifestyle adjustments. Xanthine oxidase inhibitors are often used as first-line drugs for HUA, including allopurinol (9) and febuxostat (10, 11). However, the side effects caused by long-term drug use, such as severe skin reactions, renal toxicity, need to be paid attention to (12–14). In addition, HUA patients can reduce SUA by adjusting lifestyles. Studies have shown that a healthy lifestyle including dietary regulation, restriction of tobacco and alcohol, regular exercise, and weight control can reduce SUA concentration by 10%-18% or 70-90mol/L (15–17). A multi-center longitudinal study (18) showed that HUA patients who do not exercise for (<1 hour/week) their mortality increases by 27%, of which life expectancy is shortened by 4.3 years in male, and 5.7 years in female. While HUA patients who exercise for (≥7.5MET/hour/week) mortality reduces by 11%, hence life expectancy is extended by 4-6 years, which shows that adequate exercise can reduce the risk of death and extend life. In addition, a Korean cohort study (4) showed that subjects who were sedentary for ≥10 hours a day were more likely to develop HUA than subjects who were sedentary for <5 hours a day. However, several small clinical trials have found that physical exercise does not have a positive effect on SUA levels (19–22). At present, there is no uniform standard for exercise dose and intensity to prevent or treat HUA (23–25). In addition, the long-term effects of exercise therapy have not been confirmed, and need to be verified in future clinical studies.

In this study, our purpose is to explore the effect of different exercise intensities in improving SUA of patients with HUA. We will conduct a 12-month randomized controlled trial to determine the impact of low-intensity exercise and moderate-intensity exercise on HUA. We hypothesize that both low-intensity and moderate-intensity exercise can improve HUA, and that moderate-intensity exercise is more effective than low-intensity exercise in improving HUA.

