### Randomized Allocation and Blinding

After the baseline assessment, the study will use a 1:1:1 ratio to randomly divide the subjects into 3 groups. The random table will be provided by the Statistics Department of the School of Public Health, Fudan University (Excel software; Microsoft). The test will be completed by unrelated personnel, and the random table will be kept by the main investigator. The researcher will conceal the distribution in an opaque envelope, which can only be opened after the subject has completed the baseline assessment. At the same time, this study is a single-blind randomized trial. In this study, all subjects will be unaware of the allocation of the control group, low-intensity exercise group, and moderate-intensity exercise group. The concentration of uric acid in serum and urine will be measured in Zhongshan Hospital affiliated with Fudan University. The measured values of SUA will be hidden from the investigator and patient to maintain a blind assignment.

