#### Mathematical Statistics

The data collected in the experiment will be statistically analyzed by SPSS 25.0, and the results will be expressed in the form of mean ± standard deviation. According to the specific values of each index, the Kolmogorov-Sminov test is used to determine whether it conforms to the normal distribution. If the index conforms to the normal distribution, the independent sample T-test is used to judge the difference between the two groups, and the paired sample T-test is used to judge the difference between each group before and after the intervention. If the index does not conform to the normal distribution, the Mann-Whitney test in the non-parametric test is used to judge the difference between the two groups, and the Wilcoxon test is used to judge the difference before and after the intervention in each group. Spearman correlation analysis is used to test the correlation of each index. P= 0-0.05 is set as the significance level.

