## Discussion

Studies have shown that the improvement of SUA level helps reduce the risk of chronic disease, such as hypertension (28, 29), obesity (30), diabetes (31–33), insulin resistance (34, 35).

Several small clinical trials have evaluated the effect of short-term physical exercise on SUA in HUA patients. Shu Yuan and his colleagues reported that the SUA of a 45-day aerobic exercise program (1600-meter jogging) decreased by 10.5% (P <0.05) (27) This is consistent with the findings of J Strength Cond Res et al. They reported that patients with mild to moderate high blood pressure in men with 60-79% maximum heart rate reserve for 8 weeks of aerobic exercise, SUA reduced by 41.8% (P <0.05) (36). However, another study showed that 12 weeks of strength training increased the SUA of patients with type 2 diabetes (P <0.001) (37). The study by Li-Ling Huang et al. (20) showed that the SUA level of professional athletes was significantly increased after short-term high-intensity training (P <0.05). The mechanism may be reduced uric acid excretion after high-intensity exercise, which in turn leads to an increase in SUA. Therefore, low and medium exercise may be a suitable choice to improve HUA.

This study is a randomized, multi-center, parallel trial, which aims to explore the impact of low- and moderate-intensity exercise on HUA. The expected results of this study are (1): Low-intensity exercise (brisk walking for 150 min a week, 57-63% maximum heart rate) would have a significant decrease in SUA at 6 and 12 months for HUA patients (2). Compared with the control group and the low-intensity exercise group, the moderate-intensity exercise group (jogging for 150 min a week, 64-76% maximum heart rate) would have a greater reduction in SUA levels at 6 months and 12 months (3); Low-intensity exercise and moderate-intensity exercise can significantly improve body weight, waist circumference, fat composition, blood sugar, liver function, and other chronic diseases. These results can provide a basis for the current physical activity guidelines for HUA’s healthy lifestyle management.

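### Four unranked SUA primary outcomes at three visits, compared by two-group tests at 0.05 in a three-arm trial, push the primary false-positive rate well above 5%

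*Protocol article*

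**What the plan says.** All references are to the Protocol article.

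- **Primary Outcomes** lists "The concentration of SUA, the amount of concentration change (mg/dL), the rate of change (%), and the proportion of patients with SUA concentration" at or below 7.0 mg/dL (men) or 6.0 mg/dL (women), and adds that these "from baseline to the 3rd, 6th, and 12th months will be observed". No outcome and no visit is ranked above another. The Abstract also lists four SUA outcomes as primary.
- **Randomized Allocation and Blinding** states that "the study will use a 1:1:1 ratio to randomly divide the subjects into 3 groups".
- **Hypotheses.** The Abstract's discussion paragraph expects that "both low-intensity and moderate-intensity exercise would improve HUA as compared with no-exercise control". The Background adds that "moderate-intensity exercise is more effective than low-intensity exercise in improving HUA". Together these need low versus control, moderate versus control, and moderate versus low.
- **Mathematical Statistics** states that under normality "the independent sample T-test is used to judge the difference between the two groups", and otherwise "the Mann-Whitney test in the non-parametric test is used to judge the difference between the two groups". The significance level is 0.05. The section gives no three-group test and no order among the comparisons.
- **Sample Size Calculation** uses an F test for three groups at α 0.05 and power 0.80. It gives 159 subjects (53 per group), raised to 186 for 15% loss to follow-up.

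**The concern.** The 5% error rate and 80% power in the sample-size section belong to one three-group F test. The analysis section does not use that test. It describes two-group tests at 0.05, to be applied to four primary outcomes at three visits in a trial with three hypothesised contrasts. No single comparison decides the trial, so a positive primary result could be claimed from whichever metric, visit or pair falls below 0.05. This matters because the article intends the findings to inform physical activity guidance for hyperuricemia.

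**Working it through.** **1. The plan's own figure.** The article does not state the effect size behind 159. A one-way F test with k = 3, α = 0.05 and an assumed f = 0.25 needs N = 159, with power 0.805, which matches exactly. Allowing for 15% loss, 159/0.85 = 187.1, close to the stated 186. So the stated error rate and power fit one omnibus test.

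**2. Counting comparisons.** Outcomes × visits × pairs = 4 × 3 × 3 = 36. Mathematical Statistics names no test specific to proportions. Its rule for non-normal indices would send the proportion to Mann-Whitney, but if the proportion is not tested the count is 3 × 3 × 3 = 27. The three pairs are inferred from the arms and hypotheses, because the section speaks only of two groups.

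**3. Upper reference.** If m tests were independent, the chance of at least one P<0.05 would be 1 − 0.95^m:

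- m = 36: 1 − 0.95^36 = 0.842
- m = 27: 1 − 0.95^27 = 0.750
- m = 3: 1 − 0.95^3 = 0.143

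These overstate the risk, because the outcomes are re-expressions of one measurement and the visits are correlated.

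**4. Allowing for the correlation.** All outcomes were computed from one simulated SUA series (baseline plus three visits, 53 per arm) under the complete null. The proportion was compared by a two-proportion test, a close large-sample equivalent of Mann-Whitney on a 0/1 variable. The documents give no SUA mean, SD or between-visit correlation, so these were assumed and varied. The mean was about 8 mg/dL and the SD about 1 (0.8 and 1.6 also tried). Correlation ran from 0 to 0.9, exchangeable or AR(1), with baseline truncated or not at the entry cut-offs. The ranges below span all runs.

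| Family of tests | Number | Chance of at least one P<0.05 |
|---|---|---|
| All outcomes, visits and pairs, two-sided | 36 | 0.52-0.62 |
| Same, without the proportion | 27 | 0.42-0.50 |
| Exercise versus control pairs only | 24 | 0.46-0.50 |
| Four outcomes at month 12 | 12 | 0.25-0.32 |
| SUA level at three visits | 9 | 0.19-0.33 |
| SUA level at month 12 | 3 | about 0.12 |
| All 36, hypothesised direction only | 36 | 0.31-0.39 |
| 27, hypothesised direction only | 27 | 0.23-0.30 |

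With 62 per arm and correlation 0.6, the 36-test figure was 0.57. The within-group before-after tests that the article also plans are not counted.

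**5. The remedy.** For month-12 SUA, a three-group F test followed by pairwise tests at 0.05 only if it is significant gave a family-wise error of 0.044-0.055. This is a closed procedure: with three arms, any two true pairwise nulls imply that all three arms are equal, so the omnibus test is the only intersection to be tested. If all 36 tests stayed primary, Bonferroni would need 0.05/36 = 0.0014 per test.

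**The case against.** **A separate analysis plan may handle multiplicity.** This is a condensed article, and an adjustment or post-hoc procedure is often left to the analysis plan. The F test in the sample-size section suggests that an omnibus step was at least contemplated. So the documents do not establish that no adjustment exists. What stands is what the article itself fixes: an unranked list of primaries at three visits, and stated two-group tests at 0.05 that do not match the test used for sizing.

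**A reader might infer that a false-positive primary result is more likely than not.** This does not hold generally. It needs the proportion to be tested and significant results to be counted in either direction. Without the proportion the range is 0.42-0.50. The hypotheses are directional, and counting only results that favour them gives 0.31-0.39 for all 36 tests. For month-12 SUA alone the directional figure is about 0.06-0.07, against 0.025 per test in that direction. Support for all three hypotheses at once, choosing any metric and visit for each, arose in under 1% of null trials. Inflation remains on every count.

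**A reader might infer that the article contradicts itself on the deciding visit.** The Discussion expects that the moderate-intensity group "would have a greater reduction in SUA levels at 6 months and 12 months". That is a forecast, and its visits are a subset of those in Primary Outcomes, so there is no contradiction.

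**The outcomes are one variable re-expressed.** This is true, and it is why the simulated figures, not 0.842, are the ones to use.

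**Conclusion.** The point holds. As written, the plan allows up to 36 primary comparisons (27 without the proportion), each at 0.05. The chance of at least one two-sided false positive is about 0.52-0.62 (0.42-0.50 for 27), or 0.31-0.39 for 36 in the hypothesised direction only. The narrowest reading, one metric at one visit with three pairs, still gives about 0.12, or 0.12/0.05 = 2.4 times nominal.

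These figures assume no difference between arms at any visit, the SUA parameters given above, no adjustment beyond the article, and that any one significant result would be called positive. The size depends on those assumptions. The direction does not: every reading examined exceeds the nominal rate.

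**What to change.** **Primary Outcomes.** Name one primary outcome at one visit, for example SUA concentration at month 12, the end of the intervention, adjusted for baseline. Make the other SUA metrics and the month-3 and month-6 values secondary. Another metric or visit could be defended; what matters is that one is fixed in advance.

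**Mathematical Statistics.** Compare the three arms first with the three-group F test on which the sample size rests (for the baseline-adjusted outcome, the F test for group in that model). If the rank-based branch is used, replace it with Kruskal-Wallis. Make the three pairwise comparisons at 0.05 only if the overall test is significant.

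**Cost.** Two sections need rewording, and the registration may need a matching change (its content is not available here). No extra subjects or visits are needed. Trial Status places the trial in pre-recruitment preparation, so the change can precede any data. The downside is that three current primary metrics and the earlier visits become secondary, and a pairwise difference cannot be claimed when the overall test is not significant.
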